### Interim analyses (21b)

The inclusion procedure for the SWAT can be defined as an interim analysis. Participants in their third week of treatment will be requested to respond to the questionnaires listed under column T2, Table 2. At the end of the third week, responses to the PHQ-9 and the GAD-7 are extracted and compared to baseline (T0) and T1 responses on these questionnaires. The algorithm for calculation of lack of benefit is conducted separately for the PHQ-9 and the GAD-7, such that scores on at least one of these measures that are equal to or less than 0, regardless of the participant’s chosen treatment track, lead to SWAT randomization ([PHQ-9_TO_ + PHQ-9_T1_/2] − PHQ-9 _T2_ ≤ 0) and/or ([GAD-7_TO_ + (GAD-7_T1_)/2] − GAD-7 _T2_ ≤ 0). This procedure means that the inclusion procedure for the SWAT is broad and that individuals who have improved in one type of symptom but have not improved, or worsened, in the other, can be randomized to an ATS. No other interim analyses will be conducted at this timepoint.

Regarding stopping rules, no such rules have been stipulated in advance. However, we will monitor suicide thoughts weekly via item 9 in the PHQ-9. Participants who respond with a score of ≥ 2 will be contacted by telephone for a dialog about any need for additional help. The rationale for this procedure is that external events (e.g., failing an exam) can trigger a higher score on this item, and it can thereafter decline in the next weekly measure. If a need arises for a participant to seek additional help, we will refer them and will discuss whether or not they will continue in the trial. See under “Relevant concomitant care permitted or prohibited during the trial (11d)” for further details concerning safety procedures and relevant concomitant care during the trial.

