### Eligibility criteria (10)

The inclusion criteria for the main trial are as follows: self-report of mild to moderate depression and/or anxiety, operationalized as a score of at least 5 and up to and including 19 points on the 9-item Patient Health Questionnaire (PHQ-9) [29]; and/or a score of at 5 or more points on the 7-item General Anxiety Disorder questionnaire (GAD-7) [30]. The SWAT inclusion criteria are listed under SPIRIT item 11b.

The exclusion criteria for the main trial are, in the following order:Current engagement in psychological treatment; and/orHaving initiated medication for depression and/or anxiety within the 3 weeks prior to completing the recruitment questionnaire.Scores that are (a) below (too mild) or (b) above the inclusion thresholds on PHQ-9 or GAD-7 (too severe). The latter participants are asked to provide their telephone number to the study management if they would like a telephone counseling session with the PI or co-PI; orScores of 2 or 3 on the suicidal ideation item 9 in the PHQ-9; orScores on the DSM-5 CCSM short-form questionnaire [31, 32] of (a) 3 or more on the DSM-5 suicide question (domain VI, item 11), (b) and/or scores of 2 or more on one or both of the DSM-5 psychosis questions (domain VII, items 12 and 13); (c) and/or scores of 3 or more on one or both of the DSM-5 alcohol/drug questions (domain XIII, items 21 and 23).

Participants who fulfil exclusion criteria 1 or 2 do not complete the PHQ-9 and GAD-7. Participants who do not fulfill exclusion criteria 3 or 4 complete the DSM-5 CCSM short-form questionnaire for further assessment of exclusion criteria 5a-c.

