21. *TIC-P* Healthcare consumption and productivity loss in patients with a psychiatric disorder (56 items); Bouwmans et al., 2013 [56]

22. *CSQ* Client Satisfaction Questionnaire (8 items), Attkisson & Zwick 1982 [57]

22.1. *CSQ, adapted* Client Satisfaction Questionnaire (8 items), adapted for mid-Tx assessment

23. *NEQ* Negative treatment effects questionnaire (20 items), Rozental et al. 2019 [58]

24. *Qualitative interview* Qualitative interview on experience of treatment intervention

The algorithm will build on data from the PHQ-9 and GAD-7 questionnaires, where data for all three timepoints will be entered for each questionnaire separately, as follows: [(T0 + T1)/2] − T2. If the outcome of the algorithm is equal to £0 for either PHQ-9 or GAD-7, or both, the participant will be randomized to the ATS, or to continue in the treatment arm to which they were assigned at the start of the main trial. See under “Interim analyses (21b)” for a more detailed description. Randomization will be conducted via SPSS version 28.0 using an outcome of the exact number of randomized individuals, stratified by group allocation to guided or unguided treatment. Participants with missing data at any of these timepoints will not be included in the SWAT since unsuccessful attempts will have already been made to encourage them to respond, and dropout from the main trial seems likely.

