### Criteria for discontinuing or modifying allocated interventions (11b)

Lack of short-term benefit from the intervention will constitute the inclusion criterion for the SWAT. Lack of short-term benefit will be operationalized as lack of improvement or worsening of symptoms according to PHQ-9 and/or GAD-7, measured in the third week of treatment, for participants in both the guided and unguided arms. Participants eligible for SWAT participation will be included in a secondary randomization procedure. Those randomized to the ATS will receive additional human guidance if originally randomized to the guided arm, or will be given standard guidance through written secure messages, if originally randomized to the unguided arm. Participants not randomized to the ATS will continue in the original allocation to guided or unguided treatment, without any added support. Participants in the waitlist group will not be included in the SWAT.

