### Sample size (14)

We calculated the required sample size based on the smallest effect size on primary outcomes that we did not want to miss, with respect to the contrast between the guided intervention and waiting list control at 6 months post-randomization (T4). We estimated this effect size to 0.3 Cohen’s *d*. With a significance level of 0.05 (alpha) and power of 0.8 (beta), a two-sided *t*-test would require 176 individuals per group, giving a total of 528. Assuming an attrition rate of 40% at T4, this means that we should recruit at least 880 participants. Notwithstanding this power calculation, we hope to extend our recruitment sample to up to 1200 participants if possible, given additional possible attrition after T4 and the importance of reporting outcomes over a longer term than 6 months.

Regarding analysis of the SWAT comparing adapted versus continued standard treatment for at-risk participants, earlier work evaluating for insomnia [33] suggests that between-group differences in final scores corresponding to *d* = 0.4 are possible, which would require *n* = 100 + 100 at-risk participants, i.e., well within the recruitment target.

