## Trial status

Recruitment for a pilot study, reported separately, was completed on October 19, 2021. Recruitment for the main trial began in mid-March 2022 and will continue until statistical power is estimated to have been achieved. The current protocol is version 3, dated January 30, 2024.

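### The SWAT entry formula in Interim analyses (21b) halves only T1, contradicting the averaged rule given elsewhere and failing to flag a scale that is unchanged above zero

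*Protocol article*

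**What the plan says.** The protocol states the SWAT entry rule in three places.

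- **Procedure for inclusion in the SWAT** gives the algorithm for each questionnaire "as follows: [(T0 + T1)/2", closes the bracket and subtracts T2. A result at or below zero on PHQ-9, GAD-7 or both leads to the second randomization. (The sign before the zero is garbled in the text; 21b shows that ≤ is meant.) This section points to Interim analyses (21b) for the fuller description. It also says: "Participants with missing data at any of these timepoints will not be included in the SWAT".
- **Interim analyses (21b)** says that qualifying values "lead to SWAT randomization ([PHQ-9_TO_ + PHQ-9_T1_/2", then closes the bracket, subtracts T2 and compares with ≤ 0. The GAD-7 expression has explicit parentheses around T1 alone before the division by 2. The prose of the same section describes entry as wide and says that "individuals who have improved in one type of symptom but have not improved, or worsened, in the other, can be randomized to an ATS".
- **Criteria for discontinuing or modifying allocated interventions (11b)** gives the rule in words: "Lack of short-term benefit will be operationalized as lack of improvement or worsening of symptoms according to PHQ-9 and/or GAD-7".

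The planned size of the SWAT, in Sample size (14), is "100 + 100 at-risk participants".

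**The concern.** The section named as the detailed reference carries a different rule from the section that refers to it. Read literally, 21b compares T2 with the whole T0 score plus half of T1, which is about one and a half times the baseline level. A score that has not moved then counts as improvement, and so does a moderately worse one.

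This rule is the entry criterion for a second randomization. It decides which participants in the guided and unguided arms can receive added support, and it defines the population of the SWAT analysis. If 21b were followed, most participants with an unchanged or moderately worse score would be left out, and the SWAT would be much smaller than intended.

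**Working it through.** **Inputs.** T0 is the eligibility screening score, T1 the pre-treatment score and T2 the week-3 score. The rule is applied to PHQ-9 and GAD-7 separately, and a value ≤ 0 on either one qualifies.

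**The two forms**

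- Form A (procedure section): A = (T0 + T1)/2 − T2
- Form B (21b): B = T0 + T1/2 − T2
- Difference: B − A = T0/2

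T0 cannot be negative, so B ≤ 0 implies A ≤ 0. Form B can only exclude people whom form A would include, never the reverse.

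**Unchanged score.** With T0 = T1 = T2 = s, A = 0 for every s (flagged) and B = s/2 (not flagged for any s above zero): 2.5 at s = 5, 5 at s = 10, 9.5 at s = 19.

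**Threshold.** With T0 = T1 = s, form A flags T2 ≥ s and form B flags T2 ≥ 1.5s. At s = 10 these are 10 and 15.

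| T0 / T1 / T2 | Form A | Form B |
|---|---|---|
| 10 / 10 / 10 | 0, flagged | +5, not flagged |
| 10 / 10 / 14 | −4, flagged | +1, not flagged |
| 10 / 10 / 15 | −5, flagged | 0, flagged |
| 12 / 10 / 13 | −2, flagged | +4, not flagged |
| 5 / 5 / 7 | −2, flagged | +0.5, not flagged |
| 5 / 5 / 8 | −3, flagged | −0.5, flagged |
| PHQ-9 19 / 19 / 27 | −8, flagged | +1.5, not flagged |
| GAD-7 15 / 15 / 21 | −6, flagged | +1.5, not flagged |
| 0 / 0 / 0 | 0, flagged | 0, flagged |
| 1 / 1 / 2 | −1, flagged | −0.5, flagged |

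**Ceiling.** Assuming 0–3 item scoring, the maxima are 9 × 3 = 27 and 7 × 3 = 21. Eligibility criteria (10) admits "a score of at least 5 and up to and including 19 points on the 9-item Patient Health Questionnaire (PHQ-9"). At a stable PHQ-9 of 19, form B needs T2 ≥ 28.5, which cannot occur. On GAD-7 the same happens from T0 = T1 = 15, which needs 22.5.

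**Score combinations.** Over all integer triples with PHQ-9 T0 5–19 and T1, T2 0–27, form A flags 6300 and form B 3835. For GAD-7 with T0 5–21 and T1, T2 0–21, the counts are 3740 and 1694. No triple is flagged by form B alone. These are counts of combinations, not expected proportions of participants.

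**Illustrative flag rates.** The protocol gives no score distributions, so these rest on assumptions:

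- PHQ-9 mean 10, SD 4.8; GAD-7 mean 8, SD 4.6
- retest correlation 0.6–0.8; between-scale correlation 0.5–0.65
- improvement of 1–2 points by T2
- multivariate-normal scores, rounded and truncated, kept if T0 is at least 5 on either scale and PHQ-9 is at most 19

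Over 18 settings of 400,000 draws each, form A flags 35.8–57.5% and form B 6.2–19.9%. The ratio of B to A is 0.17–0.35.

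**Expected SWAT size** = recruits × 2/3 × proportion with complete T0, T1 and T2 × flag rate. The active arms hold 880 × 2/3 ≈ 587 or 1200 × 2/3 = 800 participants.

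| Recruits | Completeness | Form A | Form B |
|---|---|---|---|
| 880 | 60–90% (assumed) | 126–304 | 22–105 |
| 880 | 100% | 210–338 | 36–117 |
| 1200 | 60–90% (assumed) | 172–414 | 30–143 |
| 1200 | 100% | 286–460 | 50–159 |

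For example, the low end for form A at 880 recruits is 587 × 0.6 × 0.358 ≈ 126. The planned 100 + 100 itself reproduces: d = 0.4, two-sided 5% and 80% power give 99.08, so 100 per arm.

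**The case against.** The strongest reply is that the document resolves the matter itself. The procedure section is clearly bracketed, the verbal definition in 11b agrees with it, and so does the prose of 21b. Nothing supports form B as an intended rule, and the two expressions in 21b are not even bracketed alike, which suggests careless setting. This stands as an account of how the error arose. It does not give the rule one reading, because 21b is the section to which the reader is sent for detail. Text extraction does not explain the error either, since the GAD-7 expression has closed parentheses around T1 alone.

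Three further points stand as limits:

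- Nothing shows that form B was ever applied, so the smaller SWAT is conditional on its having been used.
- The flag rates depend on assumed inputs. Form A can also fall below 200 when many data are missing, so a shortfall could not be blamed on the formula alone.
- The failure is per scale, not always per participant. Someone stable at PHQ-9 10 and GAD-7 0 would still enter under form B through the 0/0/0 on GAD-7.

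**Conclusion.** The concern holds. The formula in 21b is wrong as written: it contradicts the averaged formula, the definition in 11b and its own section's prose. The exact size is T0/2 on each scale, or 5 points at T0 = 10, and this needs no assumption. With T0 = T1 above zero, an unchanged score is never flagged and T2 must reach 1.5 times baseline.

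Under the assumed distributions, form B would select roughly a sixth to a third of the participants whom form A selects, and it stays below 200 in every setting tried. A misplaced bracket is the most likely cause, and the document does not show which form was used. The primary contrasts follow the original randomization, so the effect on the main trial is indirect. Because this is the threshold for a randomization, it must be corrected.

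**What to change.** In Interim analyses (21b), print [(T0 + T1)/2] − T2 ≤ 0 for PHQ-9 and for GAD-7, bracketed identically and matching the procedure section.

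The protocol records that "Recruitment for the main trial began in mid-March 2022", so SWAT randomizations may already have taken place. Confirm that the calculation applied since then, in whatever software, used the averaged form. Report any participants who were classified otherwise.

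The cost is one bracket per scale and a check of the calculation. No new data are needed.

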### Methods for additional analyses (e.g., subgroup analyses) (20b)

#### Mediator models

We will estimate the mediated effects of the guided and unguided interventions (vs. waiting list) with respect to two potentially mediating factors (behavioral activation-depression and managing negative thoughts). We will use a causal inference framework, using Bayesian inference to estimate the natural direct effect and natural indirect effect (as per the definitions of Pearl [60]). We will report on the posterior distributions of these two effects. For each primary outcome (anxiety and depression), we will estimate mediation models for each mediator separately, as well as one model with both mediators. Mediator measures will be standardized and modeled using linear regression, using the same adjustments as in the primary outcome models (i.e., outcomes measured at baseline, age, gender, and a binary variable indicating HBTQ). The mediation models will estimate both the mediated effects from T2 mediators to T3 outcomes, and T3 mediators to T4 outcomes.

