#### Procedure for inclusion in the SWAT

Participants will be included in the SWAT and randomized to the ATS when a risk of not benefitting from treatment is identified. The threshold for identifying risk will be calculated based on an algorithm that includes data from Timepoint 0 (T0; baseline trial eligibility screening), T1 (pre-treatment assessment), and T2 (mid-treatment assessment during the third week of treatment); see Table 2 for an overview of questionnaires included at each timepoint.

**Table 2 Tab2:** Overview of instruments used in treatment (Tx) RCT Sweden. Inspired by Weisel et al. 2019 [36]. All followups are timed from the point of pre-Tx randomization

Nr	Phase	Category	Construct	Instrument	T0 Tx eligibility assessment	T1 Pre-Tx Assessment	Weekly during Tx	T2 Mid-Tx after 3rd Tx module	T3 End of Tx (8 w)	T4 6 m follow-up	T5 12 m follow-up	T6 24 m follow-up
1	Screen	Mental health	Demographic / mental health screen	WHO-WMH-ICS	Data from 1st term						3rd term	5th term
1.1	Information	Referral	Referral	Resources	√							
2	Screen	Tx now?	Exclusion	3 Qs	√							
2.1	Screen	Mental health	Co-morbidity	DSM-5 CCSM +	√			√	√	√	√	√
3	Screen/Weekly/ primary outcome	Mental health	Depression	PHQ-9	√	√	√	√	√	√	√	√
4	Screen/Weekly/ primary outcome	Mental health	Anxiety	GAD-7	√	√	√	√	√	√	√	√
5	Screen (as long as relevant)	Mental health	Pandemic-related anxiety	GAD-7COVID	√							
6	Screen + all phases	Wellbeing	Well-being	WHO-5	√	√	√	√	√	√	√	√
7	Pre-Tx	Tx prep	Motivational component	Telephone interview		√						
8	Pre-Tx	Tx prep	Tx expectancy	CEQ		√		√				
9	Pre-Tx	Tx prep	Attitudes towards professional help	ATSPPHS		√					√	√
10	Mid-Tx assessment	Risk factor	Risk factor Sleep	ISI		√		√	√	√	√	√
11	Mid-Tx assessment	Skill	Behavioral Activation Depression	BADS		√		√	√	√	√	√
12	Mid-Tx assessment	Skill	Managing negative thoughts	SOCT-P		√		√	√			√
13	Mid-Tx assessment	Txprocess	Tx alliance	WAI-SR for internet Tx				√	√			
14	Secondary outcome	Wellbeing	Quality of life	WHOQOLBref		√					√	√
15	Secondary outcome	Risk factor	Alcohol	AUDIT-C		√			√	√	√	√
16	Secondary outcome	Risk factor	Risk factor Self-esteem	RSES		√			√	√	√	√
17	Secondary outcome	Risk factor	Risk factor Resilience	CD-RISC-25		√			√	√	√	√
18	Secondary outcome	Risk factor	Emotion regulation	DERS-16		√			√	√	√	√
19	Secondary outcome	Risk factor	Worry	PSWQ		√			√	√	√	√
20	Secondary outcome	Risk factor	Personality	BFI-10		√					√	√

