#### Secondary outcomes

The trial also has nine secondary outcomes, assessed in all participants regardless of treatment received. Following the same rationale as for the primary outcomes contrasts among all three groups will be done using measures at T3 and T4, while T5 and T6 measures will be used to contrast guided and unguided groups (adjusted for baseline measures). All secondary outcomes are listed in Table 2 in order of chronological administration to participants.Externally and behaviorally oriented outcomesAlcohol consumption, which will be measured using AUDIT-C (T3-T6).Comorbidity, which will be measured using DSM-5 CCSM (T3-T6).Resilience, which will be measured using CD-RISC-25 (T3-T6).Sleep, which will be measured using ISI (T3-T6).Well-being, which will be measured using WHO-5 (T3-T6).Internally oriented outcomesEmotional regulation, which will be measured using DERS-16 (T3-T6).Personality, which will be measured using BFI-10 (T3-T6).Self-esteem, which will be measured using RSES (T3-T6).Worry, which will be measured using PSWQ (T3-T6).Mediator outcomesBehavioral activation-depression, measured using BADS (T2-T3).Behavioral activation-depression, measured using BADS (T2-T3).

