## Analysis

### Statistical methods for primary and secondary outcomes (20a)

We will keep participants in the groups to which they were randomized in all analyses (intention-to-treat). We will conduct both available data analyses and analyses with missing data imputed using multiple imputations with chained equations (generating 200 datasets using 30 iterations of predictive mean matching). Both available data and imputed data analyses will be used to interpret findings.

All models of primary and secondary outcomes will be estimated using both Bayesian inference and maximum likelihood estimation [59]. The former will estimate the posterior distribution over effect estimates, while the latter will be used for null hypothesis testing. We will use (half) Student’s *t* priors for covariates, fixed intercepts, and error terms (centered at 0, with a scale of 2.5 and 3 degrees of freedom). Adaptive intercepts in multilevel models will be given standard normal priors. For point estimates, we will report the median of the posterior distribution of each parameter of interest (i.e., group contrasts), along with 95% compatibility intervals defined by the 2.5 and 97.5% percentiles of the posterior distributions. We will use the posterior probability of effect and *P*-values for our scientific inference.

The two co-primary outcomes, anxiety and depression, will be standardized and modeled using a multilevel linear regression model. The models will include a time-by-group interaction with time modeled as a dummy categorical variable (0 = T3, 1 = T4, 2 = T5, 3 = T6), as will group (0 = waiting list, 1 = unguided, 2 = guided). The models will be adjusted for baseline (T1) measures of the outcome variables (respectively) using a baseline-by-time interaction term and further adjusted for age, gender, and a binary variable indicating HBTQ (0 = No, 1 = Yes). Adaptive intercepts will be added to the models at the participant and university level. The linear combination of coefficient estimates for the group and time-by-group covariates will be used as effect estimates (i.e., differences between groups at the different follow-up intervals). For our primary contrasts (guided vs. waiting list and unguided vs. waiting list), we will report effects at T3 and T4. For our exploratory contrast (guided vs. unguided), we will report effects at all four follow-up intervals.

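### The mediation models' stated adjustment set leaves out the T1 value of the mediator, which is collected, so the natural indirect effects could be confounded

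*Protocol article*

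**What the plan says.** The section on mediator models sets the contrasts: "We will estimate the mediated effects of the guided and unguided interventions (vs. waiting list) with respect to two potentially mediating factors". The two factors are behavioural activation (BADS) and managing negative thoughts (SOCT-P). The estimand is fixed by "using Bayesian inference to estimate the natural direct effect and natural indirect effect", for two lags: T2 mediator to T3 outcome, and T3 mediator to T4 outcome.

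On covariates it says "Mediator measures will be standardized and modeled using linear regression, using the same adjustments as in the primary outcome models" and then spells the set out: "i.e., outcomes measured at baseline, age, gender, and a binary variable indicating HBTQ". In the primary models (Statistical methods, 20a) the matching statement is "The models will be adjusted for baseline (T1) measures of the outcome variables (respectively) using a baseline-by-time interaction term". There the outcome variables are GAD-7 and PHQ-9.

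Table 2 schedules both mediators at T1. Row 11 ("Behavioral Activation Depression", BADS) is ticked from T1 to T6. Row 12 (SOCT-P) is ticked at T1, T2, T3 and T6.

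On who is measured at T2, Interim analyses (21b) says "Participants in their third week of treatment will be requested to respond to the questionnaires listed under column T2", and the Table 2 column label ties T2 to the third treatment module. The Secondary outcomes section opens by saying that its nine outcomes are assessed in everyone whatever treatment they received, and its list ends with "Behavioral activation-depression, measured using BADS (T2-T3", printed twice. The data collection plan (18a) includes a mid-treatment assessment without limiting it to any arm.

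**The concern.** Natural direct and indirect effects can be read causally only if no confounder of mediator and outcome is left unadjusted. Randomisation balances the arms, which protects the effect of arm on mediator and of arm on outcome. It does nothing for the association between mediator and later symptoms within arms. A student's starting level of activation or cognitive skill is an obvious common cause. It carries over into the later mediator score, and it may act on later symptoms over and above baseline symptoms. If it is left out, stable differences between people can be counted as treatment mechanism, and the direct effect moves by the same amount the other way.

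A second, conditional question is whether the waitlist has T2 mediator values at all, since the T2-to-T3 models compare each intervention with the waitlist.

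**Working it through.** **Plan's own figure.** The mediation section states none. The trial's sample size (176 per group, 528 in total, 880 after 40% attrition) reproduces for d = 0.3 with a two-sided t-test, but it has no bearing on this point.

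**Inputs.** From the protocol: the adjustment set, the two lags, and the T1 schedule of BADS and SOCT-P. The documents give no path values, so all of these are assumptions, in SD units:
- a = 0.3, effect of arm on the later mediator
- b, effect of the later mediator on the outcome, 0.3 in size (negative, because more skill means fewer symptoms); the true indirect effect is then 0.3 × 0.3 = 0.090 in size
- q = 0.5, size of the baseline mediator-symptom correlation
- r = 0.4, 0.6 or 0.8, stability from baseline to later mediator
- g = 0, 0.1, 0.2 or 0.3 in size, path from the baseline mediator to the later outcome given the later mediator and baseline symptoms, with the same sign as b

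Baseline symptoms are assumed to reach the later mediator only through the baseline mediator.

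**Formula.** In a linear model adjusted for arm and baseline symptoms but not for the baseline mediator, the bias in b is

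g × r(1 − q²) / [r²(1 − q²) + (1 − r²)],

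and the bias in the indirect effect is a times that. With q = 0.5, 1 − q² = 0.75.

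- r = 0.4: 0.30 / (0.12 + 0.84) = 0.3125
- r = 0.6: 0.45 / (0.27 + 0.64) = 0.4945
- r = 0.8: 0.60 / (0.48 + 0.36) = 0.7143

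Multiplying by g and by a = 0.3 gives the overstatement of the indirect effect in SD (in brackets, relative to 0.090):

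| r | g = 0 | g = 0.1 | g = 0.2 | g = 0.3 |
|---|---|---|---|---|
| 0.4 | 0 | 0.009 (10%) | 0.019 (21%) | 0.028 (31%) |
| 0.6 | 0 | 0.015 (16%) | 0.030 (33%) | 0.045 (49%) |
| 0.8 | 0 | 0.021 (24%) | 0.043 (48%) | 0.064 (71%) |

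The absolute bias does not depend on b, so the same amounts would appear if the true indirect effect were zero.

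**Simulation check** (N = 1,000,000, r = 0.6, g = −0.2, true direct effect −0.15). With the T1 mediator omitted, the indirect effect is −0.119 and the direct effect −0.122. With it included, they are −0.089 and −0.152. The arm-to-mediator effect is 0.299 either way, and the total is −0.241 either way. The error lies in how the total is split.

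**T2 in the waitlist.** Suppose T2 mediators existed only in treated participants. The arm indicator (treated vs waitlist) would then be constant in the data that feed the T2-to-T3 models. A design with intercept, arm, mediator and baseline outcome has rank 3 of 4, so the effect versus waitlist is not identified. The T3-to-T4 models use no T2 mediator and are unaffected by this.

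**The case against.** **The adjustment set can be read more kindly.** Baseline outcomes might mean the baseline of each model's own dependent variable, and the Secondary outcomes section does class BADS as a mediator outcome. On that reading the mediator regression already contains the T1 mediator. This is fair, but it does not help where it matters. The vulnerable coefficient comes from the outcome regression, whose dependent variable is PHQ-9 or GAD-7, and the T1 mediator is still absent there.

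**The bias is conditional.** This stands. It is zero when g = 0, and no path value can be taken from the documents. A reader might infer that the plan will report mediation where none exists; the documents support only that it could. Nor does the simulation show that the T1 mediator would make the estimates unbiased, since it contains no other confounder.

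**T2 data in the waitlist may well exist.** A reader might infer from the treatment-worded T2 request that the indirect effects versus waitlist cannot be estimated. The documents do not establish that. The sentence in 21b describes entry to the SWAT, from which the waitlist is excluded anyway. T3 also carries a treatment-worded label, yet it is used for all three arms. The Secondary outcomes section and 18a do not restrict T2 by arm, and the schedule figure is not shown. The contrary evidence is itself weak. The five external and four internal outcomes already make nine, so the mediator lines fall outside that count, and SOCT-P is not listed there at all. The text is unsettled on this point.

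**This is an additional analysis in a condensed article.** That limits its weight, and the primary contrasts are untouched. But the article does not leave the covariates to a later document; it spells the set out.

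**The repeated BADS line is clerical.** Agreed. SOCT-P is not lost as a mediator, because the mediation section names its construct and Table 2 schedules it.

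**Conclusion.** The point holds in a conditional form. The stated adjustment set omits a collected baseline covariate that is a plausible confounder of mediator and outcome. The natural indirect effects at both lags are therefore open to a bias that randomisation does not remove. Under the assumed paths the overstatement runs from 0 to about 0.06 SD, at most about 71% of an assumed true indirect effect of 0.09 SD. It depends on g having the same sign as b; with the opposite sign the indirect effect would be understated.

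Non-identifiability is a separate, conditional matter. It applies only to the T2-to-T3 models versus waitlist, and only if the waitlist is not assessed at T2.

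**What to change.** Name the T1 value of the mediator as a covariate in both the mediator regression and the outcome regression, and use both T1 mediators in the joint model. This costs one or two covariates already collected and can be specified at any time before analysis. It reduces this source of confounding but not all mediator-outcome confounding, and the report should say so.

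Reconcile Table 2 and 21b with the Secondary outcomes section and 18a by stating whether the waitlist completes BADS and SOCT-P at T2. If it does not, drop the T2-to-T3 mediation versus waitlist or limit that lag to guided versus unguided; the T3-to-T4 models can stay. This costs a sentence or two of text and, if the data are absent, one planned contrast.

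Replace the second BADS line in the Secondary outcomes list with SOCT-P.
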